### 2.2. Family Recruitment and Eligibility

The Spanish families will be recruited by researchers from the Nutrition and Health Unit (Eurecat, Reus) and the Center for Research in Agri-Food Economics and Development (CREDA, Barcelona), and the Turkish and Moroccan families will be recruited by researchers from the Bursa Uludag University and the Unité de Nutrition et al.imentation CNESTEN, respectively. In addition, all countries will have the support of schools, high schools, family associations, and other collaborators such as primary care centers and community centers.

Families will be eligible to participate if they meet the following criteria: (a) families from any socioeconomic status with at least one child younger than 12 years and one adolescent older than or equal to 12 years (overall age range 3–17 years) and that live together; (b) informed consent has been signed by parents and the adolescent; and (c) families have a mobile phone, tablet, or computer with internet access. This inclusion criterion of composition of families and ages of children was selected to capture a range of developmental stages within families, as younger children and adolescents may respond differently to dietary interventions than adults. While this may introduce differences in family structure, it also promotes interaction across ages, potentially enhancing the adoption of healthy eating habits through sibling influence and parental support.

Exclusion criteria will be as follows: (a) having allergies or food intolerances to any of the following plant-based snack ingredients: fruit, vegetables, legumes, cereals, seeds, nuts, and yogurt (only for children under 12 years); (b) disliking any of the snack products (only for children under 12 years); (c) MD Adherence Score (MEDAS) or KIDMED score greater than or equal to 11 points, which is a food pattern already highly concordant with the MD [36]; (d) following a vegan diet (any of the family members); (e) following a prescribed long-term and strict diet for any reason, including diets for weight loss and diets for chronic metabolic or autoimmune disorders such as type 1 diabetes, celiac disease, inflammatory bowel disease, or rheumatoid arthritis (any of the family members); (f) participating in or having participated in a clinical trial or nutritional intervention study in the last 30 days prior to inclusion in this study; (g) no or limited access to the internet; and (h) being unable to follow the study guidelines.

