The educational activities will be part of an educational program specially designed to improve adherence to the MD of adolescents. The program will be conducted outside of school hours during the 3-month intervention and will be previously designed during Phase 1 of this study under the umbrella of three selected topics: (1) Mediterranean Diet and Lifestyle: discovering cultures, foods, and tastes; (2) Mediterranean Diet: from a healthy diet to a sustainable dietary pattern; and (3) Food Lab: kitchens from research or cooking centers as experimental hands-on zones for the application of healthy and sustainable dietary patterns. At least two cocreation sessions will be organized in each study country, with adolescents assigned to the educational activity groups as cocreators. The World Cafe Methodology [37,38,39] will be applied, encouraging participants to talk to each other and discuss the three selected topics in small groups in a cozy café-style space hosted by researchers as moderators (Ms) and high-school teachers as facilitators (Fs). Each session will take around one-and-a-half hours and will be joined by about 12 adolescents and at least 2 teachers and 2 researchers who will be neutral and encourage participation. The adolescents will be divided into three tables (4 to 5 adolescents per table) and, at each table, one of the three selected topics will be discussed so that the adolescents will rotate around every 20 min to participate in the discussion of all the topics (Figure 3). The researchers will record all the conversations that take place on a smartphone and will also take written notes. Once all the discussion rounds have finished and after a coffee break, the entire group will meet again in plenary. The resulting activities from each table will be summarized by researchers who will bring down the number of generated ideas to a handleable minimum, focusing on those factors generally considered to be the most important. Finally, the participants will vote on the results to prioritize actions to be implemented as educational activities in the frame of the educational program. After the cocreation session, all the data will be gathered and analyzed by the researchers in each country. The codesigned activities will then be reprioritized by all participants via an online survey. Lastly, the researchers will select and develop the 12 most voted educational activities, with 4 per topic, to be implemented within the framework of the intervention study.

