### 2.4. Visits and Procedures

All families will attend the school facilities or at research centers where they are recruited on 3 different occasions (V0, V1, and V2). The visits will be divided between the two study phases previously described. Figure 4 shows the schedule of each visit, which will follow the same timeline for each enrollment center.

In Phase 1, families will be recruited and a preassessment visit will be carried out (V0). At this point, families will be assessed against the eligibility criteria and then informed about this study in a group session. The informed consent document will be signed by parents and adolescents. The researchers will then instruct them on the completion of online questionnaires at home through the Microsoft Forms web-based application to assess socioeconomic, sociodemographic, lifestyle, and environmental indicators. This information will be valuable in predicting selected behavior sub-domains that will be evaluated based on a theoretical model derived from the COM-B model for behavior change. A theoretical model based on information on physical activity, food habits, lifestyle, and social behavior will be created, aiming to achieve the best outcomes via surveys that are not too long [41]. In addition, families will complete a 7-day semi-weighted food record (7DWR) to assess dietary habits and consumption patterns at baseline. After V0, the selected families will be randomly allocated to the different intervention/control groups.

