In Phase 2, the selected families will attend V1 and V2 at the beginning and end of the 3-month intervention study, respectively. In V1, families will receive group training according to the different intervention groups: on the use of the S2H app, on snack consumption, and/or on the use of educational materials and activities. In addition, each family will be visited individually by expert nutritionists who will assess adherence to the MD through the MEDAS and KIDMED questionnaires for adults and children, respectively, and will take anthropometric measurements (body weight, height, BMI, waist circumference, blood pressure, and heart rate) for each family member. Nutritionists will also complete a medical history, including the use of medications and/or supplements. At the end of V1, time will be left for families to self-complete online questionnaires through the Microsoft Forms web-based application. The questionnaires will be adapted according to the age of the family members to assess socioeconomic, lifestyle, dietary, and environmental indicators. In addition, families will complete a 7DWR and report food expenses during the week after V1.

During the 3-month intervention, families will use the different educational components and products. They will be in continuous contact with the research team to ensure compliance and report any adverse events, particularly in children assigned to consume the snack products. In V2, each family will be visited individually, the same parameters as those in V1 will be measured by nutritionists, and data on socioeconomic, lifestyle, dietary, and environmental indicators will be self-reported by each family member by means of online questionnaires. A closing session of this study will be carried out by researchers once the intervention is completed to inform the families of the main results of the study.

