### 2.10. Statistical Analysis

#### 2.10.1. Univariate Data Analysis

The data obtained from families in this study will be evaluated via an intention-to-treat (ITT) analysis, including data from families who drop out of the study, and per protocol (PP), that is, those families who have completed the treatment plan and who have exactly followed the instructions of the trial protocol. The error level of 0.05 will be set as a limit of statistical significance. A data analysis will be performed using the Statistical Software for Data Science (STATA, College Station, TX, USA) version 17.0 [63].

Mean and standard deviation will be reported for normally distributed variables and quantiles (25th percentile, median, and 75th percentile) for non-normally distributed variables. The Kolmogorov–Smirnov test and the Shapiro–Wilk test will be used to test for the normality of variables. The resulting scores of adherence to the MD (measured from the MEDAS and KIDMED questionnaires) will be used to calculate the mean differences between each intervention group and the control group before (V1) and after interventions (V2). Multiple comparisons (V2 vs. V0 and V2 vs. V1) of mean differences before and after interventions will be undertaken to assess the independent effect of interventions. The normality of the differences will be checked and, depending on the results, the following contrasts will be performed: parametric statistics (three-factor ANOVA with post hoc tests using the Bonferroni correction and considering the interactions between the following factors: app, educational materials, and snack products) will be used for normally distributed variables to compare differences in means and nonparametric statistics (Kruskal–Wallis test) will be used for non-normally distributed variables. Lineal regression and Spearman’s method will be used to test for correlations between normal and non-normal outcome variables, respectively.

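### The primary MEDAS/KIDMED score is analysed as unadjusted change against two reference visits, with no single primary contrast and no stated pre-randomisation baseline

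*Protocol article*

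**What the plan says.** **Analysis.** Section 2.10.1 plans "Multiple comparisons (V2 vs. V0 and V2 vs. V1) of mean differences before and after interventions will be undertaken". The differences go into a "three-factor ANOVA with post hoc tests using the Bonferroni correction", with app, education and snack as factors, or into a Kruskal–Wallis test if they are not normal. No baseline covariate is named. The same section also computes "mean differences between each intervention group and the control group before (V1) and after interventions (V2", so V1 is treated as the pre-intervention value.

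**V0.** Section 2.4 checks eligibility at V0 and then describes online questionnaires "to assess socioeconomic, sociodemographic, lifestyle, and environmental indicators", plus a 7-day food record. MEDAS and KIDMED are not named among the V0 measures. Section 2.2, however, excludes a "MD Adherence Score (MEDAS) or KIDMED score greater than or equal to 11 points". Randomisation follows V0 (Sections 2.4 and 2.6).

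**V1.** Section 2.3 says that families learn their group at the training held at the start of Phase 2, in month 10. Section 2.4 states: "In V1, families will receive group training according to the different intervention groups". It then adds an individual visit by nutritionists "who will assess adherence to the MD through the MEDAS and KIDMED questionnaires for adults and children". The self-completed online questionnaires come at the end of that visit.

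**Before V1.** Section 2.3.2 runs at least two co-creation sessions per country while the activities are being designed in Phase 1, "with adolescents assigned to the educational activity groups as cocreators".

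**The concern.** A change score needs a reference value that the allocated group cannot have influenced. V0 meets that condition, but the text does not say that a MEDAS/KIDMED score is retained from it. V1 does not meet it by design. It falls months after allocation, neither families nor staff are blinded (Section 2.6), and the score is taken at the visit where each family learns its group and is trained for it. Some education-arm adolescents have by then discussed Mediterranean-diet topics for about an hour and a half because of their assignment.

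If any of this raises the reported score in active arms, part of the effect sits in the value being subtracted. With two reference visits and no order of priority, the trial can also report two primary answers, one including about 10 months without intervention and one not. Finally, raw change gives away precision that adjustment for a score already collected would recover.

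**Working it through.** **1. The plan's own figure.** Section 2.7 gives a 1-point difference, SD 1.19, alpha 0.05, power 80%, 45 families per group, and 60 after 25% drop-out. One reading that reproduces this exactly is a two-sided comparison of two means with Bonferroni for all 28 pairs of eight groups: 2 × (3.124 + 0.842)² × 1.19² / 1² = 44.5, so 45; 45 / 0.75 = 60; 8 × 60 = 480. No stated figure is wrong. The point concerns what is compared.

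**2. A lift at V1.** Let b be the arm-specific rise in the V1 score relative to control, when the true V2 difference is 1 point.

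- V2 − V1 estimates 1 − b.
- V2 adjusted for V1 estimates about 1 − r·b (equal variances, correlation r).
- V2 adjusted for V0 estimates 1, because V0 precedes randomisation.

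The table gives power for V2 − V1 at 45 per group, taking 1.19 as the SD of the analysed difference. All values of b, and r = 0.5, are assumptions.

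| b | V2 − V1 estimates | V2 adjusted for V1 estimates | Power, 28 comparisons | Power, 7 comparisons |
|---|---|---|---|---|
| 0 | 1.00 | 1.000 | 80.6% | 90.3% |
| 0.05 | 0.95 | 0.975 | 74.6% | 86.4% |
| 0.10 | 0.90 | 0.950 | 67.9% | 81.5% |
| 0.20 | 0.80 | 0.900 | 52.6% | 69.1% |
| 0.30 | 0.70 | 0.850 | 36.9% | 54.0% |

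**3. Reach of co-creation.** Two sessions of about 12 adolescents give about 24 per country. Four of the eight groups contain education: 4 × 20 = 80 families per country. 24 / 80 = 30%, if each session draws different adolescents, one per family. More sessions would raise this; repeat attenders or siblings would lower it. The direct effect would be on adolescents' KIDMED, not on parents' MEDAS.

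**4. Precision from the same baseline.** With equal variances σ² and correlation r, change has variance 2σ²(1 − r) and ANCOVA σ²(1 − r²). The ratio is (1 + r)/2: 0.65, 0.75 and 0.85 for assumed r = 0.3, 0.5 and 0.7. If 1.19 is the SD of a single score, the families needed per group (28 comparisons) are 63 for change against 41 for ANCOVA at r = 0.3, 45 against 34 at 0.5, and 27 against 23 at 0.7.

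**5. Precision across baselines.** V0 is older, so the gain in step 4 does not carry over to a comparison of V2 adjusted for V0 with V2 − V1. For example, r = 0.3 with V0 gives 1 − 0.09 = 0.91σ², while r = 0.7 for V1 gives a change variance of 2 × 0.3 = 0.60σ². V0 adjustment still never does worse than V2 − V0 and, apart from the degree of freedom spent, never worse than an unadjusted V2 comparison.

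**The case against.** **The V0 baseline is not shown to be missing.** A reader might infer that no MEDAS/KIDMED exists at V0. The documents do not support that: eligibility is checked at V0 and exclusion (c) needs a score, and the schedule of outcomes by visit is in Figure 4, which is not available here. What remains is that the visit text does not say that this score is kept as the V0 value for each member.

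**V1 is not shown to be contaminated by the training.** Section 2.4 joins training and scoring without fixing their order, and the end-of-visit timing applies only to the online questionnaires. Same-day training could shift reporting but hardly habitual intake. All families are trained and controls receive guidelines, so part of any shift may cancel. This stands: it is a risk of unknown size. That V1 follows randomisation, and follows co-creation in the education arms, is however stated.

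**Raw change is not the only calculation.** Section 2.10.1 also compares each group with control at V2, which subtracts no baseline and is unaffected by a lift at V1. This also stands, but it adds a further candidate for the primary result.

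**The V0–V1 gap is not itself a bias.** Drift over those months is common to randomised groups, so V2 − V0 remains a fair between-group comparison.

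**Covariates are often left to the analysis plan.** That is a fair reply to silence. Here the article commits to two unadjusted difference contrasts and calls V1 the value before intervention, so a later plan would have to change what is written.

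**Conclusion.** The point holds as a defect in how the primary contrast is fixed, not as proof of a biased baseline. The plan names two unadjusted change contrasts without choosing one, does not state that the pre-randomisation score is retained, and relies on a V1 score taken after allocation, at the visit where groups are disclosed and trained.

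Any arm-specific lift at V1 reduces V2 − V1 by the same amount. The documents give no way to estimate that lift, and the power losses in the table only illustrate assumed values. The 15–35% lower variance for ANCOVA against raw change from the same baseline rests on equal variances and assumed correlations of 0.7 to 0.3. The 30% reach of co-creation rests on the minimum number of sessions and on different adolescents from different families.

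**What to change.** 1. State in Sections 2.4 and 2.5 that the MEDAS/KIDMED scores used for exclusion (c) at V0 are recorded for every family member and form the pre-randomisation baseline.
2. In Section 2.10.1, replace the two raw-change comparisons by one primary contrast: the V2 score in the three-factor model, adjusted for the V0 score (ANCOVA or the mixed-model equivalent).
3. At V1, complete MEDAS/KIDMED and the online questionnaires before group disclosure and training. Use the V1-adjusted analysis as a sensitivity analysis only: reordering the visit cannot undo co-creation or its implied disclosure to the adolescents invited.

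**Cost.** The V1 visit must be reordered and the analysis text revised; the V0 scores are already needed for eligibility. The main downside is that V0 is about 10 months older than V1, so its correlation with V2, and hence the precision gain, may be smaller. On the other side, V0 scores exist for families lost in the gap before V1, a loss that the Discussion itself expects. The change to V1 must be made before that visit takes place, because a score taken after training cannot be recovered.

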To evaluate the overall effect of the intervention as well as the individual and combining effect of each intervention component, a full-factorial design will be used [34]. This design will allow us to evaluate the independent effect of the different intervention components versus the control group and, simultaneously, the summatory effect of combining different components on increasing the family adherence to the MD. This will therefore provide a stronger inference about the effect on the different implemented interventions [35].

The overall study duration will be 13 months for each participating family, including 3 main visits (V0, V1, and V2) (Figure 2). A prior preassessment visit will be performed at baseline, followed by the intervention study that will be deployed in the last 3 months (between month 10 and 13). According to this timeframe, this study will be arranged in two different phases (Figure 2).

*Phase 1* (*month 0 to month 9*): preassessment. The families will be recruited and included in this study; they will be randomly assigned to the different study groups; and consumption patterns and sociodemographic, socioeconomic, and environmental indicators will be evaluated through specific questionnaires. In addition, the different educational materials and activities, AI-based app, and healthy plant-based snacks will be developed prior to the start of the intervention study. This information will help us understand the context of each participant group and inform our analysis.

*Phase 2* (*month 10 to month 13*): the intervention study will be deployed at the family level. Families will receive the educational materials and activities, the AI-based app, and the plant-based snacks developed in Phase 1, depending on their assigned intervention group. In addition, anthropometrics, lifestyle, dietary, and socioeconomic and environmental indicators will be evaluated through specific questionnaires.

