### 2.5. Outcomes

The primary outcome will be adherence to the MD measured through the MEDAS and the KIDMED questionnaire score in parents and children, respectively. The MEDAS is an extension of a 9-point score developed in the Prevención con Dieta Mediterranea (PREDIMED) trial [42,43]. It consists of 2 questions about eating habits, 8 questions about the frequency of consumption of typical foods of the MD, and 4 questions about the consumption of foods not recommended in this diet. Each question is scored with 0 (noncompliant) or 1 (compliant), and the total score ranges from 0 to 14, so a score of 14 points means maximum adherence. The KIDMED score consists of 16 items with affirmative or negative answers, where there are 4 questions denoting a negative connotation to the MD and 12 questions denoting a positive connotation. A positive answer to questions denoting negative connotation is scored with −1, while positive connotation questions are scored with +1. The total score ranges from 0 to 12, so a score of 12 points indicates good adherence [44]. To avoid deviations in outcomes (such as physical activity or portions of food), surveys will be assessed by researchers during visits.

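### A preliminary normality test selects the analysis of MEDAS and KIDMED, and its non-normal branch (Kruskal–Wallis) cannot deliver the factorial effects the trial was designed to measure

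*Protocol article*

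**What the plan says.** Section 2.10.1 (Univariate Data Analysis) names two normality tests: "The Kolmogorov–Smirnov test and the Shapiro–Wilk test will be used to test for the normality of variables". For the MEDAS and KIDMED changes it then sets a switch: "The normality of the differences will be checked and, depending on the results, the following contrasts will be performed". If the differences pass, the analysis is a "three-factor ANOVA with post hoc tests using the Bonferroni correction and considering the interactions between the following factors"; by these it means the three components. If they fail, "nonparametric statistics (Kruskal–Wallis test) will be used for non-normally distributed variables". No factorial method is named for that second branch.

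Section 2.1 gives the reason for the design in a sentence that begins: "To evaluate the overall effect of the intervention as well as the individual and combining effect of each intervention component, a full-factorial design will be". It adds: "This design will allow us to evaluate the independent effect of the different intervention components versus the control group".

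Section 2.5 defines the two scores by counting items. For MEDAS, "the total score ranges from 0 to 14, so a score of 14 points means maximum adherence". For KIDMED, "The total score ranges from 0 to 12, so a score of 12 points indicates good adherence". One person's score, and so one person's change, is therefore a whole number. The Discussion takes the family as the unit of analysis, and the article does not define a family-level score.

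**The concern.** The two branches answer different questions. The ANOVA splits the differences among eight arms into three main effects, three two-way interactions and one three-way interaction. Kruskal–Wallis over eight arms gives one overall p-value and no such split. Run one factor at a time it gives a marginal test of that factor, but still no interaction test and no effect estimate.

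If the differences fail the check, a trial built as a full factorial would therefore report its primary outcome without the factorial analysis. The check is prone to fail, because whole-number changes depart from a normal curve through their discreteness alone. The article also leaves open whether normality is tested on pooled data, by arm or on residuals, and what happens if the two tests disagree. The analysis of the primary outcome is thus not determined in advance, and MEDAS and KIDMED could end on different branches.

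**Working it through.** **Inputs.** Section 2.7 gives alpha 0.05, beta 0.20, SD 1.19, a difference of 1 MEDAS point, 45 evaluable families per arm (360 in all) and 60 recruited (480). It does not say whether 1.19 is the SD of a score or of a change. If it is the SD of a score and the two visits were uncorrelated, the change would have SD 1.19 × √2 = 1.68. SDs of 2.0 and 2.5 are assumptions added to show the range.

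**Step 1: the plan's own figure.** With Bonferroni over all 28 pairs of eight arms, alpha = 0.05/28, and n = 2(z₁₋α/₂ + z₀.₈₀)² SD²/Δ² = 2 × (3.124 + 0.842)² × 1.19²/1² ≈ 44.5, so 45 per arm. Then 45/0.75 = 60, 45 × 8 = 360 and 60 × 8 = 480. The stated figures are reproduced.

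**Step 2: how often normality is rejected.** Changes were simulated as normal and rounded to whole points, so rounding is the only departure from normality. Both tests used the 0.05 level. Kolmogorov–Smirnov (KS) used the estimated mean and SD with standard p-values, which is conservative. SW is Shapiro–Wilk. Residuals assume 0.3 points per component; family means assume two members with correlation 0.3.

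| What is tested | n | SD 1.19 | SD 1.68 | SD 2.0 | SD 2.5 |
|---|---|---|---|---|---|
| Individual changes pooled, SW and KS | 360 or 480 | 100% | 100% | 100% | 100% |
| One arm, SW | 45 | 97–98% | 53–55% | 30–31% | 16–17% |
| One arm, SW | 60 | 100% | 76–78% | 45% | 22–25% |
| One arm, KS | 45 | 46% | 8% | 3% | 1% |
| At least one of eight arms, SW | 45 each | 100% | 99.8% | 96% | 77% |
| ANOVA residuals, SW | 360–480 | 70–82% | 39–57% | 30–38% | 18–23% |
| Family means pooled, SW | 360–480 | 100% | 100% | 100% | 69–99% |
| Family means, one arm, SW | 45 | 35% | 14% | 12% | 8% |

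A separate run agreed for individual changes: 100% pooled at 360; by arm of 45, SW fell from 98% (SD 1.19) to 18% (SD 2.5) and KS from 43% to about 2%. Choices the article leaves open thus move the rejection rate from about 1% to 100%.

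**Step 3: whether the ANOVA needs protecting.** On whole-number changes with SD 1.19 and 45 per arm (1500 runs), the seven factorial tests had type I error 0.044 to 0.063 against a nominal 0.05. The simulation standard error is √(0.05 × 0.95/1500) = 0.006. The 0.063 did not recur: in three further runs with a true effect of one component, the six null tests gave 0.039 to 0.057. The ANOVA keeps its level without the switch.

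**Step 4: what the other branch costs.** Take an assumed effect of 0.36 points for one component and none for the others. The main-effect test compares 4 × 45 = 180 families with 180. Rounding adds 1/12 to the variance, so the SD is √(1.19² + 1/12) = 1.22, the standard error is 1.22 × √(2/180) = 0.129, and power is Φ(0.36/0.129 − 1.96) ≈ 0.80. Simulation over two runs gave:

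| Test | Power |
|---|---|
| Eight-arm Kruskal–Wallis | 0.44–0.47 |
| Eight-arm one-way ANOVA | 0.47–0.49 |
| Kruskal–Wallis on that factor alone, 180 v 180 | 0.78 |
| t-test on that factor, 180 v 180 | 0.79 |

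Like for like, ranks cost 1 to 3 percentage points. Nearly all of the gap between about 0.46 and 0.79 comes from spreading one contrast over 7 degrees of freedom.

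**The case against.** Four stronger readings are tempting, and the documents do not support them.

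- A reader might infer that normality will almost always be rejected. That holds for pooled individual changes, and for Shapiro–Wilk by arm at SD 1.19. It fails for most other ways of applying the rule, and a family average, which the Discussion's choice of unit may imply, need not be a whole number.
- A reader might infer a heavy loss of power from using ranks. Step 4 shows otherwise. The 0.36-point effect is also an assumption. At the protocol's own 1 point, with control 1 point below the other seven arms, the eight-arm Kruskal–Wallis had power 0.97 and the eight-arm ANOVA 0.975.
- A reader might infer that the Kruskal–Wallis branch leaves no effect estimate at all. Section 2.10.1 plans arm-versus-control mean differences before it reaches the switch. What is missing is factorial main effects and interactions.
- A reader might blame the switch for the absence of country and baseline. The ANOVA branch lists only the three components, so that absence is common to both branches.

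It is also fair that no inflation of type I error from the two-stage rule has been shown, and that a separate analysis plan may exist. The core stands: the switch is stated in the article, and an analysis plan that follows it inherits a branch with no factorial contrasts.

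**Conclusion.** The point holds in a limited form. A preliminary normality test selects the analysis of the primary outcome, and one of its two outcomes removes the interaction tests and factorial main-effect estimates that Section 2.1 sets as the aim. Arriving on that branch is likely, not certain. The rejection rates assume changes that are normal before rounding; skewness or ceiling effects in real scores could add to them. The loss is of the contrasts themselves, not of statistical efficiency, and at 45 per arm the ANOVA does not need the safeguard. The conclusion that the fallback cannot answer the factorial question needs no simulation: it follows from setting Sections 2.1 and 2.10.1 side by side.

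**What to change.** In Section 2.10.1, delete the normality switch for MEDAS and KIDMED. State that the three-factor linear model (app, education, snack and their interactions) is the primary analysis whatever the distribution, with robust or bootstrap intervals. If individual members are analysed, cluster on family; if one score per family is analysed, use heteroscedasticity-robust standard errors and define that score. Keep residual plots as diagnostics that do not change the analysis. If a distribution-free check is wanted, add a permutation test of the same factorial contrasts as a sensitivity analysis.

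This takes about one paragraph, with no extra data and no change to the sample size, and should be settled before anyone sees outcome data by arm.
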